### Participants, eligibility, and recruitment

This study seeks 50 individuals who are newly enrolled in a community-based weight loss program centered in a metropolitan area of a Midwest state. Participants will be recruited from an existing 6-month-long community-based weight management program hosted by the University of Kansas Medical Center, local Diabetes Prevention Programs and other behavioral weight loss programs in the local area that may range from 6 to 12-months long. These weight management programs typically include trained health educators, 1-hour weekly video meetings, group peer support, structured nutrition plan (low calorie diet), personalized activity recommendations, and behavior change modifications [15]. Prospective participants will be recruited at their initial consultation or orientation visit for their behavioral weight loss program. Flyers will also be presented to participants at their initial visit. Measures were planned to coincide with initial enrollment (week-0), early weight change (week-6), and later weight change measures (week-12, week-26).

To be included, participants must be newly enrolled or plan to enroll in a community-based weight management program, must be over 18 years of age, have body mass index (BMI) ≥30 m/kg^2^, own a smartphone and be willing to download the mobile application to receive text messages [16]. Participants who chose to cease their community-based weight management program involvement after enrolling in the INSTANT study can still participate in later assessments, improving upon past studies which only included individuals who completed their program [17,18]. Indeed, stress may impact continued engagement in a weight management program. Participants will be excluded for being currently prescribed FDA-approved medications for weight loss, treatment for a medical condition that could affect body weight, or impacting stress levels (e.g., antidepressants), a current psychological condition that is untreated, hospitalization for a psychological condition within the past 12-months, or not being on a stable dose of treatment for at least 6-months. Other exclusion criteria are not being fluent in writing or speaking the English language, mobility limitations so they are unable to perform physical activity, and a family member who was previously enrolled or is currently enrolled in the study.

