#### Primary outcome: Weight.

Participants’ height (cm) and weight (kg) will be objectively measured by a trained research assistant using standard operating procedures, such as shoes removed, with a mounted stadiometer and portable scale. Measurements will be taken in duplicate and an average was used. If the measurements differed by more than 0.5 units, then a third measurement was taken. Body mass index (BMI, weight/height^2^, kg/m^2^) will be calculated. Weight at Visits 2−4 will be subtracted from Visit 1 (Week-0) to calculate change in weight.

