### Analytical approach

#### Aim 1: Examine the association between variability in individual stress and weight change.

For hypothesis 1a, that high variability in daily stress will be related to less weight loss, linear regression will examine week-0 average and change frequency in daily stress (morning survey) with weight change at week-12 (visit 3) and week-26 (visit 4). For hypothesis 1b, that high variability in daily stress will be related to less physical activity and sleep, multi-level models with logit link function (and binomial distribution) will be used to examine association between week-0 morning stress and same day MVPA and sleep, with an interaction of time/day*morning stress. For exploratory analyses, we will examine the associations of daily stress with MVPA and sleep at other time points (week-6, week-12, and week-26), lagged day effects of stress (i.e., stress on day 1 influencing MVPA and sleep on day 2) to preserve temporal ordering and considering inverse probability weighted marginal structural models, and the outcome of weight change at week-6.

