#### Aim 2: Examine the association between variability in coping and positive affect and weight change.

To address hypothesis 2, that high variability in coping and positive affect will be related to less weight loss, linear regression will examine week-0 average and change frequency in coping (morning survey) and positive affect (within day survey) with weight change at week-12 and week-26.

Potential covariates for both models include number of ACEs, program compliance (i.e., number of sessions attended), coping mechanisms (number and type), age, and sex. Statistical significance will be set at *p* = 0.05. All available data will be analyzed with a sensitivity analysis for individuals with complete data. Significant weight loss will be seen at 12-weeks (12.7 ± 19.9 kg), and 6-months (12.7 ± 35.2 kg) based on past studies in our community-based weight loss program allowing us to compare weight loss in Hypothesis 1a and 2. [15]

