#### Sample size and power calculation.

Based on past EMA work (*n* = 39), there was an association between daily morning stress and feeding practices (*p* = 0.01) [52]. Considering physical activity and sleep are also impacted by stress [10,11], we anticipate being able to detect an association between stress variability with physical activity and sleep with prescribed amount (*n* = 50). This amount will allow us to compute a random linear regression model with 0.80 power, 0.3 effect size, 0.01 alpha error probability, 0.27 lower critical R^2^, and up to five predictors (such as potential covariates) [53]. Meeting minimum compliance (5-days), we would still have ≥5 observations/participant (≥250 observations) to calculate variability and detect meaningful associations.

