#### Data management plan.

All participants will be given an ID as part of the screening process. This ID will be stored on a secure database at the University of Kansas Medical Center. Only approved project staff will have access of the server. At each major time point (week-0, 6-weeks, 12-weeks, and week-26), we will collect other participant data including anthropometry (weight and height), accelerometry, questionnaires related to participant behaviors, stress, and stress-related states. Program attendance data will be collected after Visit 4. These values will be reported as tabular data and stored in a secure electronic data capture system. All subject-level clinical data will be preserved and shared. Shared data will be deidentified, and the original data will be maintained at the investigator’s institution. Completed salivary tubes will be frozen until analysis and stored at a biospecimen freezer at the local site. This data will be processed within 1-year of collection to calculate salivary cortisol, and remaining biospecimen will not be stored.

Missing data and data quality will be assessed throughout the study, including REDCap validation rules, double data entry of values (e.g., height and weight), reviewing participant salivary collection logs, and periodic review of study records. For EMA, participants are contacted multiple times during their use period to ensure compliance and any technical issues that may impact obtaining data. For accelerometry, device non-wear periods and implausible values will be identified through reviewing device wear logs and routine quality control procedures of devices. During analysis, we will examine patterns of missing data. If appropriate, mixed models will be used; these models are robust to incomplete repeated measures under a missing-at-random assumption. Further, sensitivity analyses may be considered to evaluate the impact of missing data on study findings.

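### Weight at week 26 is analysed by a single-visit change-score regression that cannot use earlier weights, and the complete-data sensitivity analysis says little about dropout

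*Protocol article*

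**What the plan says.** All references are to the protocol article.

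- **Outcome** (Primary outcome: Weight): "Weight at Visits 2−4 will be subtracted from Visit 1 (Week-0) to calculate change in weight". Each person therefore has one simple change score per follow-up visit.
- **Model** (Analytical approach, Aim 1): for Hypothesis 1a, linear regression of the week-0 stress summaries "with weight change at week-12 (visit 3) and week-26 (visit 4"). Aim 2 uses the same method for coping and positive affect. Multi-level models are assigned to Hypothesis 1b (physical activity and sleep). Week-6 weight change is exploratory.
- **Covariates** (Aim 2): a list introduced as potential names adverse childhood experiences, sessions attended, coping mechanisms, age and sex. Baseline weight and program are not on it.
- **Analysis set** (Aim 2): "All available data will be analyzed with a sensitivity analysis for individuals with complete data".
- **Missing data** (Data management plan): "If appropriate, mixed models will be used; these models are robust to incomplete repeated measures under a missing-at-random assumption". Further sensitivity analyses may be considered.
- **Source of participants** (Participants, eligibility, and recruitment): the host institution's 6-month program, plus "local Diabetes Prevention Programs and other behavioral weight loss programs in the local area that may range from 6 to 12-months long".
- **Size** (same section): "This study seeks 50 individuals who are newly enrolled in a community-based weight loss program".

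**The concern.** A regression with one change score per person at week 26 has no use for anyone not weighed then, even if that person was weighed at weeks 6 and 12. In such a model, analysing all available data is already almost a complete-case analysis. Agreement with the complete-data sensitivity analysis would therefore be no evidence that dropout is harmless.

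The protection under missing-at-random that the Data management plan describes belongs to models with several outcome records per person. The named weight analysis is not one, and the article does not say whether or when a mixed model would replace it.

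Program is also left unnamed, although week 26 is the end of some programs and about the midpoint of others. Sessions attended is hard to compare across programs unless program is in the model.

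At stake is a variability slope at week 26 that may be pulled towards zero and estimated less precisely than the collected data allow, in a small cohort.

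**Working it through.** **1. The plan's own figure.** The sample-size section gives "0.80 power, 0.3 effect size, 0.01 alpha error probability, 0.27 lower critical R^2^, and up to five predictors" for n = 50. Reading 0.3 as the population R², the exact random-predictor test with five predictors at alpha 0.01 has power 0.773 at N = 50 (critical R² 0.283). Power of 0.80 needs N = 53 (power 0.810, critical R² 0.268). The figure is thus nearly but not exactly reproduced. It concerns the overall R² test with all 50 analysed. With 20% missing at a visit, 50 × 0.8 = 40 remain, and power is 0.61 at alpha 0.01 or 0.82 at 0.05. Both levels are shown because the analysis section says "Statistical significance will be set at *p* = 0.05", which is a separate matter.

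**2. Who enters the week-26 model.** Let D26 = W0 − W26. D26 exists only if W26 was measured, so the available-case set is everyone weighed at week 26 with exposure and covariates. The complete-data set is that group or a subset of it. At week 12 the two sets can differ more, because people later missing week 26 may be excluded from the second. The Current progress section illustrates the point: one person was lost after the 3-month visit. If that person's week-12 weight was recorded, the week-26 regression still cannot use it.

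**3. Bias and precision under dropout (illustration).** The documents give no dropout rate, mechanism or within-person correlation, so all of these inputs are assumptions:

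- n = 50 and a standardised exposure;
- true slope 2 kg per SD of exposure at week 26 and 1.2 kg at week 12;
- residual SDs of change 5 kg (week 12) and 8 kg (week 26), with correlation 0.70 or 0.85;
- dropout before week 26 either completely random or logistic in week-12 change, with log-odds 1 or 2 per 5 kg.

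There were 3,000 runs per setting. Monte Carlo error of a mean slope is about 1.28/√3000 = 0.023 kg, or about 1 percentage point of the true slope. The comparison is a likelihood analysis that also uses week-12 weight.

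| Missing at week 26 | Random dropout: variance, available-case ÷ likelihood | Dropout on week-12 change: attenuation of available-case slope |
|---|---|---|
| 10% | 1.06–1.07 | 4–13% |
| 20% | 1.12–1.18 | 8–19% |
| 30% | 1.17–1.27 | 10–23% |
| 40% | 1.26–1.47 | 12–27% |

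The likelihood analysis stayed unbiased throughout, within simulation error. Under random dropout the available-case slope was unbiased too. Under the stronger dependence the precision gain nearly vanished (variance ratio 0.97–1.06), so the benefit there is removal of bias.

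Against sampling error, at 20% missing the mean available-case slope ran from 1.839 kg (SD over runs 1.281) to 1.618 kg (SD 1.202). The shift is (2 − 1.839)/1.281 = 0.13 to (2 − 1.618)/1.202 = 0.32 of a standard error.

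**4. Missingness that depends on stress only.** If the probability of being weighed depends only on variables in the regression, the conditional mean of D26 given those variables is the same in those seen and those missing. The slope is then not biased. Bias needs dependence on the weight trajectory beyond what is modelled.

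**5. Baseline weight.** With equal SDs σ and correlation ρ between W0 and W26:

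- Var(D26) = 2σ²(1 − ρ);
- residual variance given W0 = σ²(1 − ρ²);
- ratio = (1 + ρ)/2.

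For ρ = 0.80, 0.90 and 0.95 (assumed) the ratio is 0.90, 0.95 and 0.975. The reduction is 10%, 5% and 2.5% of residual variance.

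**The case against.** The strongest reply is that the article does not fix complete-case analysis. The Data management plan promises to examine missing-data patterns and allows mixed models, and this can be read as the fallback for repeated weights. Retention is also taken seriously. People who leave their program may stay in the study, data are sought after discontinuation with weight as first priority, and contacts are bi-weekly and then monthly. The remark that stress may affect engagement concerns the program, not study visits.

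Much of this stands, and it rules out several stronger readings that a reader might infer:

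- *That interim weights are ignored.* Week 12 is itself an analysis time point and week 6 is an exploratory outcome. What is true is that the week-26 estimate does not borrow from them.
- *That baseline weight and program are excluded.* The covariate list is only potential. They are unnamed, not ruled out.
- *That the slope is biased as planned, or that baseline weight buys a large gain in precision.* The bias rests on an assumed dropout mechanism and the gain is probably small. Possible confounding and program differences are the better reasons for both covariates.
- *That the complete-data analysis checks nothing.* At week 12 it can differ from the main analysis. The criticism applies mainly at week 26.

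It is also fair that, in an observational cohort, adjusting for baseline weight changes the question to change conditional on starting weight.

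What the reply does not answer is that per-visit linear regression is the named method for weight, while multi-level models are named for Hypothesis 1b. The conditional mention of mixed models has no trigger and no link to weight.

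**Conclusion.** The point holds in a limited form. The named week-26 analysis uses only people weighed then, leaves their own and others' earlier weights out of the estimate, and is paired with a sensitivity analysis that says little about dropout at that visit. The mixed-model provision does not settle the matter.

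The size is modest and conditional: about 8–19% attenuation at 20% missing if dropout follows week-12 weight change, none if it depends only on modelled stress, and at most about a third of a standard error in these settings. With random dropout the cost is variance 12–18% above that of the likelihood analysis at 20% missing.

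The change is still worth making. It uses data already collected, is valid under a weaker assumption and costs little. Nine participants were enrolled by January 2026, so it can be made well before analysis.

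**What to change.** **Primary model.** For Hypotheses 1a and 2, name one repeated-measures mixed model, fitted for each exposure, of weight at weeks 6, 12 and 26. Include baseline weight, program, visit, mean exposure, exposure variability and variability-by-visit, with an unstructured covariance across visits. Read the variability slope at weeks 12 and 26.

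**Missing data.** State that this analysis assumes weights are missing at random given the modelled variables and observed weights. Replace or supplement the complete-data analysis with a delta-adjusted one: impute missing week-26 weights under missing-at-random, shift them by a prespecified range of kilograms, and report how the slope moves. Let the shift vary with exposure in at least one scenario, because a common shift alters the slope only if missingness is related to exposure.

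**Cost.** Wording and code, no new data. Mean exposure, variability, baseline weight and a two-level program term (host or other) take four of the five predictors in the sample-size section, leaving one for the other potential covariates. These must be chosen in advance. Visit and variability-by-visit terms come on top. A two-level program term merges dissimilar outside programs, and a finer coding would cost more degrees of freedom. The slope becomes conditional on baseline weight, so the article should say that this is the intended question. The simple change-score regression can be kept as a supporting analysis.

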#### Sample size and power calculation.

Based on past EMA work (*n* = 39), there was an association between daily morning stress and feeding practices (*p* = 0.01) [52]. Considering physical activity and sleep are also impacted by stress [10,11], we anticipate being able to detect an association between stress variability with physical activity and sleep with prescribed amount (*n* = 50). This amount will allow us to compute a random linear regression model with 0.80 power, 0.3 effect size, 0.01 alpha error probability, 0.27 lower critical R^2^, and up to five predictors (such as potential covariates) [53]. Meeting minimum compliance (5-days), we would still have ≥5 observations/participant (≥250 observations) to calculate variability and detect meaningful associations.

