#### Current progress.

The current study began recruitment on March 7^th^, 2025. As of January 2026, we have enrolled nine participants, six participants have completed their week-6 visit, and four have completed their 3-month visit. One person was lost to follow up after their 3-month visit. No adverse events have been reported. We anticipate concluding recruitment in 2026, with data collection completed by February 28^th^, 2027. Descriptive and final results are expected to be published in the year 2027.

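### The power statement's figures do not fit together at n = 50, and they describe an omnibus test at another alpha, not the planned test of stress variability on weight change

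*Protocol article*

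**What the plan says.** Under *Participants, eligibility, and recruitment*, the protocol article sets the target: "This study seeks 50 individuals who are newly enrolled in a community-based weight loss program".

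*Sample size and power calculation* first argues, from an association in an earlier study of 39 people, that the investigators expect to "detect an association between stress variability with physical activity and sleep with prescribed amount (*n* = 50"). It then says that this number supports a "random linear regression model with 0.80 power, 0.3 effect size, 0.01 alpha error probability", with "0.27 lower critical R^2^, and up to five predictors (such as potential covariates"). It does not say whether the effect size of 0.3 is R², f² or a correlation. Weight change does not appear in the section.

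The analysis sections read differently:

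- *Aim 1* uses linear regression for weight change at weeks 12 and 26, with two exposure terms (the week-0 average and the change frequency of morning stress). It assigns physical activity and sleep to multi-level models with a logit link.
- *Aim 2* uses linear regression of weight change on the same two summaries of coping and of positive affect. It states: "Statistical significance will be set at *p* = 0.05". It also says: "Potential covariates for both models include number of ACEs, program compliance (i.e., number of sessions attended), coping mechanisms (number and type), age, and sex".

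**The concern.** A power statement should let the reader recover n from its inputs and should refer to the test that will decide the primary question. This one appears to do neither. The printed power and critical R² do not both belong to n = 50. A critical R² belongs to the joint test of all predictors, and that test can be significant because of age or sessions attended alone, which would say nothing about stress variability. The outcomes named are not the ones linear regression is planned for, and the alpha is not the one the analysis will use.

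At stake is how the primary result is interpreted. If the coefficient for stress variability is not significant, the only power figure available is 0.80, and it was not calculated for that coefficient or argued for weight change.

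**Working it through.** **Inputs.** From *Sample size and power calculation*: n = 50, alpha 0.01, k = 5 predictors, effect size 0.3, power 0.80, critical R² 0.27, random regression model. From *Aim 2*: alpha 0.05 and five listed covariates. From *Aim 1*: two exposure terms.

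**1. Critical R² at n = 50.** This depends only on n, k and alpha, so no reading of the effect size changes it.

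R²crit = kF / (kF + n − k − 1), where F is the upper 1% point of F(k, n − k − 1).

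- n = 50: F(5, 44) = 3.465, so 17.326 / (17.326 + 44) = 0.283
- n = 52: F(5, 46) = 3.444, so 17.221 / (17.221 + 46) = 0.272
- n = 53: F(5, 47) = 3.434, so 17.172 / (17.172 + 47) = 0.268

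The printed 0.27 fits 52 or 53, not 50.

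**2. Power of the named model.** With random regressors, the F statistic has noncentrality [R²/(1 − R²)] × χ²(n − 1), and power is averaged over that chi-square. With R² = 0.3, k = 5 and alpha 0.01:

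| n | critical R² | power |
|---|---|---|
| 50 | 0.283 | 0.773 |
| 52 | 0.272 | 0.798 |
| 53 | 0.268 | 0.810 |

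A raw-data simulation at n = 50 gave 0.772. The smallest n with power of at least 0.80 is 53.

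**3. Other readings at n = 50, alpha 0.01.**

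| Reading | power | critical R² |
|---|---|---|
| R² = 0.3, fixed regressors, k = 5 | 0.806 | 0.283 |
| R² = 0.3, random regressors, k = 4 | 0.817 | 0.251 |
| f² = 0.3 (R² = 0.3/1.3 = 0.231), random, k = 5 | 0.564 | 0.283 |
| multiple correlation 0.3 (R² = 0.09), random, k = 5 | 0.127 | 0.283 |

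No reading tried gives 0.80, n = 50 and 0.27 together. Because the metric is unnamed, the five-predictor random model can mean anything from 0.13 to 0.77.

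**4. Effect of the alpha conflict.** The same omnibus test (random, R² = 0.3, k = 5) at alpha 0.05 has power 0.917 with 50 analysed and 0.824 with 40. The 40 is an assumption; the document gives no completer count.

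**5. Predictor count.** Two exposure terms plus five listed covariates make 2 + 5 = 7, against a stated maximum of five. If all seven entered, omnibus power at n = 50 would be 0.687 at alpha 0.01 and 0.872 at alpha 0.05.

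**6. Power for the coefficient of interest.** For one coefficient with partial R² = ρ² and random regressors, the test is F(1, n − k − 1) with noncentrality [ρ²/(1 − ρ²)] × χ²(n − k), averaged over the chi-square. With fixed regressors the noncentrality is n × ρ²/(1 − ρ²). Solving for 80% power at two-sided alpha 0.05 with k = 5:

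| analysed | random: partial R² (partial r) | fixed: partial R² (partial r) |
|---|---|---|
| 50 | 0.16 (0.40) | 0.14 (0.375) |
| 40 (assumed) | 0.20 (0.45) | 0.17 (0.415) |

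**7. Outcome and model.** The power section pairs linear regression with physical activity and sleep. *Aim 1* pairs those outcomes with multi-level logit models and keeps linear regression for weight change. The calculation therefore matches the model for weight change but is argued for outcomes that will be analysed differently.

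**The case against.** The strongest reply is that little is numerically wrong. The named model gives 0.77 rather than 0.80, a difference of three participants, and the fixed-regressor formula with R² = 0.3 returns exactly 50. The alpha conflict works in the study's favour: at the planned 0.05 the omnibus test has power 0.92, and still 0.82 if only 40 are analysed. The covariates are only candidates, and the power section speaks of a maximum of five, so the model need not exceed it. All of this stands and limits the point. It does not restore the 0.27, and it does not answer the mismatch of test and outcome.

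Three stronger readings are tempting, and the document does not support them.

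- **The study is underpowered.** A reader might infer this, but power for the variability coefficient depends on a partial R² that the document does not give. Dividing the 0.30 equally among five predictors would be an assumption of the reader's own.
- **Dropout invalidates the figure.** No completer count or dropout rate is stated to compare with. The protocol keeps people who leave their weight loss program, gives priority to collecting weight and analyses all available data.
- **The calendar rules out 50.** The article reports: "As of January 2026, we have enrolled nine participants". It then says: "We anticipate concluding recruitment in 2026, with data collection completed by February" 2027. Accrual is slow, but extending it forward is a feasibility projection. It contradicts no stated recruitment date and is not an error in the power calculation.

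**Conclusion.** The point holds in a limited form. Taking 0.3 as R², the stated inputs give power 0.77 and critical R² 0.283 at n = 50; the printed pair belongs to 52 or 53. That discrepancy is minor and would not by itself matter much.

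What matters is that the 0.80 is not the power of the primary analysis. It is for an omnibus R² test at alpha 0.01, argued for physical activity and sleep, while the primary question is one coefficient, on weight change, at alpha 0.05. For that coefficient, 50 analysed participants give 80% power only if stress variability explains about 16% of the variance in weight change left after the other predictors.

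The 0.16 assumes five predictors, random normal regressors and a two-sided test (the protocol does not state sidedness). The 0.20 also assumes 40 analysed. None of this shows that 50 is the wrong number to recruit.

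**What to change.** 1. Use one alpha in *Aim 2* and in *Sample size and power calculation*.
2. Say whether the effect size is R², f² or a correlation. If the omnibus calculation is kept as a secondary statement with its present inputs, print power 0.77 and critical R² 0.28 for n = 50.
3. State power for the primary question, for example: *With two-sided alpha 0.05, five predictors and random regressors, the study has 80% power to detect a partial R² of about 0.16 (absolute partial correlation 0.40) for stress variability on weight change with 50 participants analysed, and about 0.20 (0.45) if 40 are analysed (assumed).* Use 0.14 and 0.17 only if a fixed-regressor model is named instead.
4. Make the number of predictors in the primary model agree with the power statement. With two exposure terms, a limit of five leaves room for three of the five listed covariates. If more are used, recalculate.
5. Separate the argument for physical activity and sleep from this calculation, since those outcomes have a different model.

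The cost is wording only. No extra participants or measurements are needed, but the stated figure becomes less favourable.
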